## Abstract

**Background:**

At any one time, one in every five Canadians has low back pain (LBP), and LBP is one of the most common health problems in primary care. Guidelines recommend that imaging not be routinely performed in patients presenting with LBP without signs or symptoms indicating a potential pathological cause. Yet imaging rates remain high for many patients who present without such indications. Inappropriate imaging can lead to inappropriate treatments, results in worse health outcomes and causes harm from unnecessary radiation. There is a need to understand the extent of, and factors contributing to, inappropriate imaging for LBP, and to develop effective strategies that target modifiable barriers and facilitators. The primary study objectives are to determine: 1) The rate of, and factors associated with, inappropriate lumbar spine imaging (x-ray, CT scan and MRI) for people with non-specific LBP presenting to primary care clinicians in Ontario; 2) The barriers and facilitators to reduce inappropriate imaging for LBP in primary care settings.

**Methods:**

The project will comprise an inception cohort study and a concurrent qualitative study. For the cohort study, we will recruit 175 primary care clinicians (50 each from physiotherapy and chiropractic; 75 from family medicine), and 3750 patients with a new episode of LBP who present to these clinicians. Clinicians will collect data in the clinic, and each participant will be tracked for 12 months using Ontario health administrative and self-reported data to measure diagnostic imaging use and other health outcomes. We will assess characteristics of the clinicians, patients and encounters to identify variables associated with inappropriate imaging. In the qualitative study we will conduct in-depth interviews with primary care clinicians and patients.

**Discussion:**

This will be the first Canadian study to accurately document the extent of the overuse of imaging for LBP, and the first worldwide to include data from the main healthcare professions offering primary care for people with LBP. This study will provide robust information about rates of inappropriate imaging for LBP, along with factors associated with, and an understanding of, potential reasons for inappropriate imaging.

**Electronic supplementary material:**

The online version of this article (10.1186/s12891-019-2427-1) contains supplementary material, which is available to authorized users.

## Background

Low back pain is the world’s leading cause of disability due to non-fatal health outcomes from diseases and injuries, and presents a major societal and individual burden [1, 2]. Low back pain is one of the biggest public health problems in Canada; at any one time, one in every five Canadians has low back pain [3], and it is the second most common symptom, after a cough, seen in family practice [4–6]. Each year in Canada, direct treatment costs for low back pain exceed CAD$8 billion [7], with significant additional societal costs associated with losses in worker productivity and associated disability payments.

For people with low back pain who seek care, the most common providers of choice are family practitioners, chiropractors and physiotherapists [8]. However, management of low back pain in these settings is not always concordant with recommended evidence-based practice [9–11]. Plain film x-rays are over-utilised [12, 13], and computed tomography (CT) and magnetic resonance imaging (MRI) are increasingly being utilised when not clinically indicated [11].

For patients presenting with low back pain to primary care providers, serious pathological cause is rare and up to 99% of people have “non-specific low back pain” [14]. Non-specific low back pain means pain is not attributable to a recognisable, known specific pathological cause, such as infection, tumour, fracture, or cauda equina syndrome [15]. Despite this high percentage of patients presenting with non-specific low back pain, imaging rates in the primary care setting are high [16].

Multiple international clinical practice guidelines consistently recommend that diagnostic imaging tests are not routinely indicated for people presenting with non-specific low back pain because it can lead to inefficiencies and waste in the healthcare system [17–21]. Imaging for these patients is of limited diagnostic value, provides no benefits for function, pain, or disability [22–25], may lead to worse health outcomes [26–28], and exposes people to unnecessary radiation (for x-ray and CT) [29]. Imaging may also lead to unnecessary invasive diagnostic procedures and subsequent treatment, increased waiting time for people who are in need of appropriate diagnostic imaging, poor utilisation of human resources, and excessive costs [30–33].

Despite evidence of the overuse of imaging for low back pain in other high-income countries [9, 11, 16], in Canada, there is no up-to-date information of the extent of this problem. An Ontario Institute for Clinical Evaluative Sciences (ICES) report indicated that from 1992 to 2001 the rate of CT scan and MRI use for low back pain management by family doctors in Ontario increased, along with a substantial increase in costs [34]. As well as now being out of date, this report did not determine appropriateness of imaging, nor did it examine imaging utilisation in primary care settings other than family practice. We need a better understanding of the extent of, and the factors associated with, inappropriate imaging for people with low back pain to inform effective knowledge translation interventions [35, 36].

To inform effective knowledge translation interventions relevant in Canada, we need to determine current clinician and patient beliefs. A recent systematic review of qualitative studies identified that clinicians lacked content knowledge of low back pain guidelines [37]. The few studies that have examined patient-related factors found that two out of three people had inappropriate beliefs about the use of imaging in low back pain [38–40], and most patients with low back pain expected to receive imaging [41–43]. Knowledge translation interventions are often unsuccessful because they do not adequately target the key determinants of the behaviours that need to change [44–46], whereas effective knowledge translation interventions have a strong rationale and address modifiable barriers and facilitators to the uptake of evidence-based care [47]. Thus, there is mounting evidence suggesting that the design of knowledge translation interventions requires a more systematic approach with a strong rationale for the chosen design and explicit reporting of the intervention development process [48–50].

We need a better estimate of the extent of inappropriate imaging for low back pain in Canadian primary care. We also need to obtain reliable information to inform the design of effective knowledge translation interventions to improve the quality of low back pain care. This project will provide new knowledge to inform the design of tailored strategies to reduce inappropriate imaging for low back pain. These interventions will have the potential to improve the use of healthcare resources and reduce harm to the vast number of people who seek care for low back pain in Canada.

## Methods

Our overall project goal is to inform the design of evidence-based and theoretically-informed knowledge translation strategies to reduce inappropriate imaging for people with low back pain in Ontario, targeting primary care clinicians, patients and the public. To achieve this goal, we will undertake a mixed methods study incorporating an inception cohort study (Study 1) and a qualitative study of primary care clinicians and patients (Study 2).

### Study objectives

#### Primary objectives

To determine the rate of, and factors associated with, inappropriate lumbar spine imaging (x-ray, CT scan and MRI) for people with non-specific low back pain presenting to primary care clinicians in Ontario.To determine the barriers and facilitators to reducing inappropriate imaging for low back pain in primary care settings.

#### Secondary objectives

3.To determine differences in rates of recommending imaging among types of primary care clinicians.4.To describe demographic characteristics and patterns of care for people with low back pain in primary care settings.

### Methods for study 1

#### Clinician and patient recruitment

*Clinician participants (n = 175)* will comprise 50 each from chiropractic and physiotherapy, and 75 from family medicine. We are recruiting more family medicine clinicians than the other professions because lower numbers of patients with low back pain attend family medicine than chiropractic and physiotherapy. Our partner organisations will promote study participation via their normal communication strategies to their clinician members. We will invite clinicians in community-based practices chosen randomly from the lists of all registered clinicians in Ontario. From the College of Physicians and Surgeons of Ontario we will select only family doctors. From the College of Physiotherapists of Ontario we will select only physiotherapists whose primary work site is primary care. From the College of Chiropractors of Ontario we will use the full list.

We anticipate a 30% response rate based on our previous experience [51, 52], hence we will approach at least 600 clinicians to reach our sample size. To ensure the efficient use of project resources, we will target clinicians who practice in seven geographic regions within Ontario, Canada. These regions were selected to be representative of the mix of high and low population density areas, and different geographical regions: 1) Sudbury/North Bay; 2) Mississauga/Halton (Mississauga; Oakville; Milton); 3) Kitchener, Waterloo, and Guelph; 4) London, Ontario; 5) Central Toronto; 6) Southeast Ontario (Belleville; Brockville; Napanee; Smiths Falls; Kingston; Picton; Gananoque; Perth); 7) Ottawa region (Ottawa; Kanata; Nepean; Orleans).

We will invite clinicians to participate using a modified tailored design method [53] by sending a primer postcard, an invitation letter, two reminder letters and a telephone call. We will also use a snowball sampling technique, where, after clinicians are recruited, they will be asked to approach clinicians who work in the same practice, or other clinicians they know who they believe may be interested in participating.

Recruited clinicians will complete a baseline demographic questionnaire including: sex; age; training location; years in practice; and proximity of practice to imaging facility (see Additional file 1: Appendix 1 for questionnaire). Results of this questionnaire will be used to assess clinician representativeness by comparing to available province-wide clinician demographic characteristics and also be used as clinician-related factors when modeling inappropriate use of imaging.

*Patient participants (n = 3750):* Consecutive patients with low back pain will be invited to participate until up to 25 are recruited from each participating clinician. Research staff will visit each participating practice to train the practice staff and clinicians in the study procedures. To reduce possible selection bias, we will encourage practice staff at each location to follow a strategy suitable for their practice that maximises the chances of recruiting consecutive patients with low back pain. For clinicians in solo practice without reception staff, typical of some chiropractors and physiotherapists, clinicians will approach potential participants directly. For clinicians in circumstances where practice reception staff are likely to know in advance that a patient’s consultation is for low back pain, practice reception staff will be asked to inform every such patient about the study during the recruitment period and provide them with recruitment information to read in the waiting room. If the patient consents to participate, the practice staff will inform the clinician, who will then complete the enrolment process, including screening for participation.

We are allowing 12 months for patient recruitment; that is, approximately two patients with low back pain recruited per month per clinician, which is feasible based on incidence rates of low back pain presentations in these settings [4, 54, 55]. Practices will be offered reimbursement for staff time required to recruit patients and collect data.

Rates of patient recruitment will be monitored via contact from the research team to clinicians and practice staff approximately every 2 weeks. We will ask participating clinicians to keep a de-identified list of patients whom they approached, and to indicate how many were ineligible and how many declined participation. To reduce the risk of selection bias, practice staff, clinicians and patients will only be told that this is an observational study on the current management of low back pain in primary care, and not that lumbar imaging is the main focus. There is a lower incidence of low back pain presentations in family medicine compared to chiropractic and physiotherapy, so patient recruitment in this setting will require more support [56].

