### Sample size justification

The study will be adequately powered to determine factors associated with imaging behaviour, including both clinician (e.g. profession) and patient (e.g. severity and duration of pain) characteristics. We will compare inappropriate imaging rates among professions, assuming base imaging rates across the professions range from 10 to 45% [9, 11, 34, 64, 65]. Using an intracluster correlation coefficient estimate of 0.088 [66, 67], and 25 as the cluster size (3750 total patients), this study will have at least 95% power to detect an absolute difference in imaging rates between professions of 6%. For patient factors, we hypothesise that increased pain severity and increased pain duration may be associated with inappropriate imaging [43], this study will have at least 90% power to detect a 10% difference in imaging rates with each 2-point increase in pain severity measured by the numerical rating scale (0 to 10), or each 2-week increased duration of low back pain.

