### Quantitative data analyses

Characteristics of clinicians, patients and encounters will be summarised using descriptive statistics. We will calculate imaging rates per 100 low back pain patients with 95% confidence intervals and we will determine imaging rates for each primary care profession. We will undertake multilevel logistic regression analysis to determine the effects of clinician- and patient-level factors on inappropriate imaging. Clinician-level factors assessed will include age, sex, profession type, location of clinician training, clinician years in practice, ownership of imaging facilities, knowledge of imaging guidelines, and time spent with patient. Patient-level factors measured at baseline will include age, sex, race/ethnicity, insurance status, living in a metropolitan area, beliefs about usefulness of imaging, education level, duration/severity of low back pain, and three month measurement of satisfaction with treatment and adverse events. Patients consulting each clinician will form a cluster and will be considered as the second level in the multilevel logistic regression. We will also conduct a marginal logistic regression analysis to investigate the effects of clinician- and patient-level factors on inappropriate imaging and estimate the association between inappropriate imaging and explanatory factors in the marginal model using Generalised Estimating Equations. The analysis will allow examination of differences in results from the two models and determine whether the conclusions depend unduly on the model assumptions.

### Methods for study 2

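### An overall Ontario imaging rate, calculated as the article states, would depend on the profession mix set by recruitment quotas and the patient cap

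*Protocol article*

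**What the plan says.** All places are in the protocol article.

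- **Primary objectives:** the first objective is a rate "for people with non-specific low back pain presenting to primary care clinicians in Ontario". Differences between professions are a secondary objective.
- **Clinician and patient recruitment:** the 175 clinicians "will comprise 50 each from chiropractic and physiotherapy, and 75 from family medicine". Family medicine gets the larger quota "because lower numbers of patients with low back pain attend family medicine than chiropractic and physiotherapy". Patients are invited "until up to 25 are recruited from each participating clinician". Clinicians are invited at random from registration lists, and in addition: "We will also use a snowball sampling technique". A baseline questionnaire is used to compare clinician demographics with province-wide data.
- **Sample size justification:** 3750 patients, cluster size 25, intracluster correlation 0.088, and professions are compared "assuming base imaging rates across the professions range from 10 to 45" per cent.
- **Quantitative data analyses:** "We will calculate imaging rates per 100 low back pain patients with 95% confidence intervals", and rates for each profession. Profession is also a factor in the regression models.

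**The concern.** The objective refers to people presenting to primary care across the province. A rate for that population is an average of the profession-specific rates, weighted by where Ontario patients with low back pain actually seek care. In the sample, the weights come from quotas and a cap. The reason given for the unequal quotas is ease of recruitment, not proportional representation.

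A rate per 100 enrolled patients therefore carries the sample's weights. The regression models estimate associations and do not restore the provincial mix. The representativeness check concerns clinician demographics, not each profession's share of patients. If the overall figure were read as the Ontario rate, it could be off by more than its interval suggests, and enrolling more patients in the same proportions would not reduce the error.

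**Working it through.** **Plan's own figures.** The article gives no expected overall rate and no precision for it, so there is none to reproduce. Its power statement concerns differences between professions, which do not depend on the mix, and is not used here. The patient total does matter:

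- 175 × 25 = 4375, not 3750.
- 3750 = 150 × 25 = 3 × 1250, that is, equal thirds, with 1250/75 = 16.7 patients per family doctor.
- 3750/175 = 21.4 per clinician, if all recruit equally (mix 50:50:75).

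The planned patient mix could be either. Both are set by the design.

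**Inputs.** From the article: quotas 50/50/75, 3750 patients, cluster size 25, intracluster correlation 0.088, rates within 10 to 45%. Assumed: rates of 10% (physiotherapy), 25% (chiropractic) and 45% (family medicine); the Ontario share of family medicine; the remaining share split equally between the other two.

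**Overall rate** = sum of (share × rate), shares in the order physiotherapy, chiropractic, family medicine:

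| Mix | Calculation | Overall rate | Gap from 29.3% |
|---|---|---|---|
| Sample 50:50:75 | (50×10 + 50×25 + 75×45)/175 | 29.3% | – |
| Sample, equal thirds | (10 + 25 + 45)/3 | 26.7% | – |
| Ontario, family medicine 25% | 0.375×10 + 0.375×25 + 0.25×45 | 24.4% | −4.9 |
| Ontario, family medicine 60% | 0.2×10 + 0.2×25 + 0.6×45 | 34.0% | +4.7 |
| Ontario, family medicine 80% | 0.1×10 + 0.1×25 + 0.8×45 | 39.5% | +10.2 |

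From an equal-thirds sample (26.7%) the three gaps are −2.3, +7.3 and +12.8 points.

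**Sampling interval.** Design effect = 1 + (25 − 1) × 0.088 = 3.112. Half-width = 1.96 × √(p(1 − p) × 3.112/3750):

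- p = 0.267: 2.5 points
- p = 0.275: 2.5 points
- p = 0.293: 2.6 points

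**Sensitivity to the assumed rates** (order chiropractic/physiotherapy/family medicine):

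| Rates | 50:50:75 | Equal thirds | Family medicine 20% | 60% | 80% |
|---|---|---|---|---|---|
| 10/10/45% | 25.0% | 21.7% | 17.0% | 31.0% | 38.0% |
| 45/10/10% | 20.0% | 21.7% | 24.0% | 17.0% | 13.5% |
| 45/10/27.5% | 27.5% | 27.5% | 27.5% | 27.5% | 27.5% |
| 27.5% in all | 27.5% | 27.5% | 27.5% | 27.5% | 27.5% |

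The second row reverses the direction. The third shows no gap because the family medicine rate equals the mean of the other two, which are weighted equally. The fourth shows no gap because the rates do not differ.

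**The case against.** The strongest reply is that the article never says the overall rate is unweighted. It is a condensed account, and a fuller protocol or analysis plan may specify weights. That stands: a reader might infer that an unweighted pooled estimate has been chosen, and the text does not say so. It does not remove the point, because a provincial target, a quota sample and a plain rate per 100 patients are all stated, and they do not fit together without a further step.

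The other replies limit the point.

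- The profession-specific rates are already planned. They and the comparison between professions do not depend on the mix.
- A 50:50:75 patient mix needs equal recruitment per clinician, and the stated total also fits equal thirds. With equal thirds and a 25% family medicine share, the gap is 2.3 points, inside the sampling half-width.
- A reader might take the span from 24.4% to 39.5%, about 15 points, as the error. It compares two hypothetical populations. The error is the distance from the sample's own figure.
- Shares of 60 or 80% for family medicine sit uneasily with the recruitment section, which says fewer patients with low back pain attend family medicine. That may mean per clinician, but the larger gaps rest on it.
- A reader might conclude that the overall rate has no population meaning. That goes too far: clinicians are invited at random from registration lists in seven regions, and consecutive patients are sought.
- A reader might also infer that snowball recruits push the rate further from the provincial value. The document gives no basis for the size or direction of such an effect.

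**Conclusion.** The point holds as a mismatch between objective and calculation. Followed as written, an overall rate takes its profession weights from the recruitment plan, whether the patient mix ends near 50:50:75 or near equal thirds. The article's assumption that rates differ between professions makes this matter.

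On the assumed rates of 10, 25 and 45%, the gap from the 50:50:75 figure runs from about −5 to +10 points. The sampling interval does not allow for it. These figures illustrate the problem and do not estimate a bias: the profession rates, their order and the Ontario shares are all assumptions, and the upper end needs an 80% family medicine share. Size and direction remain unknown, and the gap can be zero. The change should be made, but it concerns only the overall rate and leaves the rates by profession intact.

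**What to change.** In the Quantitative data analyses section:

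1. Name the profession-specific rates, with intervals that allow for clustering, as the primary estimates for objective 1.
2. Report an overall Ontario rate only when it is weighted to a sourced distribution of low back pain patients by profession. State the source and show the result over a range of shares.
3. If no credible source exists, label any pooled rate as a figure for the study sample.

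Repeating the rates without snowball-recruited clinicians is an optional sensitivity analysis.

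The cost is a change of analysis wording, the search for an external share, and a somewhat wider interval for the weighted rate. Recruitment need not change.

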#### Inclusion/exclusion criteria

*Clinician participants* will be currently practising and providing care for patients with low back pain. Their practice must be a first point of contact for ambulatory care in Ontario, and they must be in good standing with their respective Ontario regulatory body. We will exclude family doctors who practice in academic family health teams due to the presence of residents rotating through these practices.

*Patient participants* will be eligible if they are consulting participating clinicians for the first time for an episode of low back pain, with or without leg pain, and they have an Ontario Health Insurance Plan (OHIP) number. Patients will be included if they are aged ≥18 years old with a new episode, or acute exacerbation, of low back pain. This is defined as the current episode of pain preceded by at least four weeks without significant low back pain; we define significant low back pain when average pain intensity is scored as 3 or more on a scale of 0 to 10, and the pain interferes with daily activities. Pain will be in the region bound by the lower ribs and the lower gluteal fold, with or without pain referred beyond this region. Patients will be excluded if they are pregnant, or if they are unable to speak and read English. Where possible, practice staff will use a checklist to screen potential patients for eligibility (see Additional file 1: Appendix 2). Otherwise, participating clinicians will screen patients for inclusion at baseline.

